### Aims and Hypotheses

This randomized controlled trial assessed the common assumption that cognitive training in children should be adaptive. The trial aimed to examine children’s outcomes of working memory training using adaptive, self-select, and stepwise approaches to setting the the difficulty of training activities compared to an active control condition immediately and 6-month postintervention. Although the aim is exploratory, we hypothesized that children allocated to the working memory training conditions would show greater improvements: (1) on near transfer compared to intermediate and far transfer measures and (2) immediately postintervention compared to 6-month postintervention.

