### Statistical Analysis

Primary analyses will be intention to treat (ITT) with sensitivity analyses only with children who completed the allocated intervention. Primary analyses will be separate linear regressions for each primary outcome at the primary end point (immediately postintervention) as the dependent variable, the outcome at baseline and the stratification factor (age) as covariates, and conditions (dummy coded with the active control as the reference) as the independent variables. Statistical significance will be set at α=.05 (2-tailed). If outcomes do not meet the normality assumption, a nonparametric bootstrap will be used. Effect sizes and 95% CI will be reported to demonstrate the magnitude of differences in outcomes between each training condition relative to the active control. Bayesian methods will be used to quantify the strength of evidence in favor of the null hypothesis and the alternative hypothesis. Interpretation of results will consider the strength of effects and *P* values. The same analytic approach will be applied to secondary outcomes and to both primary and secondary outcomes at the 6-month postintervention time point.

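### Both stated hypotheses compare training effects across transfer levels or across time, but the analysis fits each outcome at each time point separately and so estimates neither difference

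*Protocol article*

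**What the plan says.** The Abstract (Objective) and the Aims and Hypotheses section give the same two expectations. The latter introduces them with "Although the aim is exploratory, we hypothesized that children allocated to the working memory training conditions would show greater improvements" and lists them as "1) on near transfer compared to intermediate and far transfer measures and (2) immediately postintervention compared to 6-month postintervention".

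The Statistical Analysis section fixes the model: "Primary analyses will be separate linear regressions for each primary outcome at the primary end point (immediately postintervention) as the dependent variable". The adjustment is for "the outcome at baseline and the stratification factor (age) as covariates", and the terms of interest are "conditions (dummy coded with the active control as the reference) as the independent variables". Effect sizes with 95% CIs are promised for each training condition against the active control. Bayesian methods are to weigh evidence for the null and the alternative, and interpretation is to consider both the strength of effects and P values. The section then extends the approach to everything else: "The same analytic approach will be applied to secondary outcomes and to both primary and secondary outcomes at the 6-month postintervention time point".

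The Power Calculations and Sample Size section covers one comparison only: each training condition against active control on near transfer immediately after the intervention.

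**The concern.** Each hypothesis is a statement about a difference between two training effects. The planned regressions give one training effect per condition, outcome and time point, and stop there. The quantity that each hypothesis names is never estimated.

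The effects to be compared come from the same children and are therefore correlated. Two separate intervals do not give the uncertainty of their difference, and two separate P values do not test it. If the report says that near transfer improved and far transfer did not, or that the benefit had faded by 6 months, that wording would rest on a comparison by eye. These are the only hypotheses the article states, so their conclusions will be read as findings of the trial.

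**Working it through.** **1. What the hypotheses need and what the regressions supply.** Let b1 and b2 be the training-versus-control effects on two outcomes, or on one outcome at two times, with standard errors s1 and s2. Both hypotheses concern b1 − b2, whose variance is s1² + s2² − 2·r·s1·s2, where r is the correlation between the two estimates. Separate regressions give b1, b2, s1 and s2 but not r, so no interval for b1 − b2 can be formed from the planned output. For hypothesis 1 the outcomes must also be on a common scale, and the article names none for this comparison.

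**2. The article's own sample size.** Inputs from the Power Calculations section: f² = 0.07, 80% power, α = .05. For a test of one regression coefficient (1 numerator df, noncentrality 0.07 × N), 80% power needs N = 115. Then 115/4 = 28.75, so 29 per condition, and at N = 116 power is about 81%. A 3-df omnibus test would need 160. The stated figure therefore reproduces as a single training-versus-control coefficient. With four equal arms f² = d²/8, so d = √(8 × 0.07) = 0.75 residual SD. The calculation is sound for its purpose and includes neither hypothesised difference.

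**3. How far separate P values can mislead (illustration).** Assumptions: identical true effects, equal power for each test, two-sided 5%, and r = 0.5 or 0.7. The documents give no r. The 80% is the design power for the primary comparison; the 60% is a lower assumed value. Each z statistic has mean 1.960 + z(power), that is 1.960 + 0.842 = 2.802 at 80% and 1.960 + 0.253 = 2.213 at 60%. The chance that the first is significant and the second is not equals power − P(both significant) under a bivariate normal:

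| Power each | r | P(both) | First significant, second not |
|---|---|---|---|
| 80% | 0.5 | 0.687 | 0.113 |
| 80% | 0.7 | 0.713 | 0.087 |
| 60% | 0.5 | 0.439 | 0.161 |
| 60% | 0.7 | 0.478 | 0.122 |

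This is for one training arm and one pair. The plan has three training arms and several pairs.

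**4. What a direct contrast could deliver.** Assumptions: effects in residual-SD units and residual correlation ρ between the two scores, again not in the documents. The SD of the within-child difference is √(2(1 − ρ)). With 29 per arm and ρ = 0.5 this SD is 1. The standard error is √(2/29) = 0.263 for one training arm against control, a 95% half-width of 1.96 × 0.263 = 0.51 SD. With the three training arms pooled (87 against 29), it is √(1/29 + 1/87) = 0.214, a half-width of 0.42 SD. Power to detect a difference in effects of 0.5 SD:

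| ρ | One arm vs control | Pooled arms vs control |
|---|---|---|
| 0 | 27% | 38% |
| 0.3 | 36% | 50% |
| 0.5 | 48% | 65% |
| 0.7 | 69% | 85% |

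For a difference of 0.25 SD (0.5 against 0.25), power over the same range of ρ is 10% to 23% for one arm and 13% to 33% pooled. The contrasts can be estimated, but with wide intervals.

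**The case against.** The aim is labelled exploratory, and the question the trial was sized for, each training condition against active control on near transfer immediately afterwards, is modelled directly. No primary estimate or error rate is touched. The plan also offers more than P values: effect sizes with CIs, Bayesian evidence for the null, and interpretation by strength of effect. An article is a condensed document, and further secondary contrasts could sit in a fuller plan. All of this limits severity. It does not remove the point, because the article does not leave the approach open: it fixes it for all outcomes and both follow-up times, and that approach yields no difference between effects.

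Two stronger readings are tempting and are not supported. A reader might infer that the plan would count a significant near or immediate effect alongside a non-significant other effect as confirmation. The Statistical Analysis section contains no such rule; the percentages above show what an informal reading risks, not what the plan prescribes. A reader might also infer that the intermediate and far tests are shorter or noisier than the near tests, which would make a false pattern likelier. The documents do not show this. The article gives reliability above 0.80 for the full Raven's and none for sets A and B alone. It gives no reliability for any near-transfer test, and those tests can end after a single block of four trials. The 2-back has 22 items, Raven's sets A and B have 24, and the ADHD-RS-5 has 18.

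**Conclusion.** The point holds, as a should-fix. Following the article exactly produces no estimate, interval or test of either stated hypothesis; they could only be judged informally from correlated effects set side by side. That conclusion is structural and needs no assumed figure.

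The size of the risk is illustrative: about 9% to 11% at 80% power each and 12% to 16% at 60%, for one arm and one pair. It rests on equal true effects and correlations of 0.5 to 0.7 that the documents do not supply. It would be wrong to conclude that the hypotheses are wholly unaddressed, since effect sizes and CIs allow a descriptive comparison, or that the primary analysis or its sample size is at fault.

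**What to change.** Keep the separate regressions for the per-outcome estimates. Add one joint model that allows for correlation within child, or a bootstrap that resamples children and refits the regressions, with two pre-specified contrasts, each with a 95% CI:

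1. The training-versus-control effect on near measures minus that on intermediate and far measures, at the immediate time point.
2. The immediate minus the 6-month training-versus-control effect on the two primary tests.

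State whether each contrast is per training condition or pooled over the three. Use a common scale that is valid for the score actually analysed. Raven's is given as sets A to E at baseline but A and B afterwards, so score sets A and B from the baseline administration; the SD of the full baseline score would belong to a different test. Align the direction of the ADHD-RS-5 with the other outcomes, and note that its recall window is 2 weeks at the immediate visit and 6 months otherwise.

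Say that the contrasts are exploratory and that the sample size was not set for them, so a non-significant difference does not show equal effects. If they are not added, state that both hypotheses will be judged descriptively only.

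The cost is one extra analysis on data already collected, which the article describes as still being processed and analysed, and intervals that will be wide.

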## Results

This trial was supported by internal research funding from the School of Psychological Sciences and the Turner Institute for Brain and Mental Health at Monash University, awarded in December 2019. Data collection was attempted in July 2021 but was ceased shortly after due to COVID-19 lockdowns in Melbourne. Data collection occurred from February 2022 to December 2022. Data are currently being processed and analyzed. It is anticipated that the results of this trial will be published by 2024.

## Discussion

The potential transfer of skills learned from a cognitive training intervention to other untrained activities is of interest to practitioners in health and education sectors, and families. Cognitive training interventions are intensive and typically comprise adaptive training activities, yet whether this approach to setting the difficulty of training activities maximizes transfer effects has only been systematically evaluated once in adults [7]. This trial aims to examine outcomes of working memory training using adaptive, self-select, and stepwise approaches to setting the difficulty level of training activities compared to an active control condition. This will be the first trial to systematically examine methods of setting the difficulty of working memory training activities in children. Our design includes evaluation of nonadaptive approaches (self-select and stepwise) and thereby eliminates task difficulty as a confounder, which was an important limitation of initial studies in the field.

This trial has important strengths. The trial design, methods, and analysis plan are in line with best-practice standards for cognitive training trials [1]. The trial was randomized, participants and assessors were blinded, and an active control condition was used. The active control condition (instead of a passive or no-contact control) was designed to be believable as an intervention, indistinguishable from the working memory training conditions in terms of the environment and motivating features, and thus was designed to ensure children experience a similar level of engagement, and experimenter and teacher attention to children allocated to the working memory training conditions. The set of outcome measures was designed to detect discrete levels of near transfer by minimizing confounders associated with training effects [4], and intermediate and far transfer effects are measured too. Training outcomes were assessed immediately postintervention and again at 6-month postintervention to determine any persisting training benefits. The trial is sufficiently powered to detect differences between the working memory training conditions and the active control condition. Importantly, our novel experimental working memory training interventions are designed specifically for this research and reflect the current understanding of the cognitive mechanisms of training: the processing demands of the training activities are (1) sufficiently unfamiliar such that the child needs to generate novel cognitive routines to do well, and the routines can then be applied to new activities that are similar but untrained; and (2) overlap with daily activities, such as following teacher directions, which overlap with daily activities. This is the first time the following instructions paradigm has been used as a working memory training activity. The nonadaptive approaches used in this trial reflect a similar approach to learning that children experience in daily activities, such as having autonomy over their learning (self-select), and mastering simpler concepts before complex concepts (stepwise). Motivation questionnaires will be used in analyses to determine if children in the training and active control conditions have similar motivation toward learning in the classroom and expectations of the intervention.

It is acknowledged that this trial was not powered to detect potential differences between the adaptive, self-select, and stepwise working memory training conditions. The lack of research and effect sizes from nonadaptive approaches makes calculating appropriate power challenging. We anticipate the differences in effect sizes between the 3 conditions will be small, and therefore a particularly large sample size would be required and this may not be practical or feasible.

This trial will determine whether the adaptive approach to setting the difficulty of working memory training activities is superior for maximizing training outcomes. It is our intention to present findings at national and international conferences and publish findings in peer-reviewed journal papers. Families and staff of the participating school will receive a summary of the findings. Findings will contribute to our understanding of the design of effective working memory training interventions, discrete levels of transfer of working memory training, and the malleability of cognitive functions in children. Knowledge gained could have implications for other types of cognitive training that target core domains such as attention and inhibitory control, and for other populations, including aging and dementia [3]. This work could help highlight the value of evidence-based principles of cognitive training and shift the focus from studying the effectiveness of different programs to more rigorous evaluations of the foundational principles of cognitive training. In summary, the results have the potential to influence the future direction and application of cognitive training.

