**Conclusions:**

This trial will determine whether the adaptive approach to setting the difficulty of training activities maximizes cognitive training outcomes for children. This trial has several strengths: it adopts best practices for cognitive training studies (design, methods, and analysis plan); uses a range of measures to detect discrete levels of transfer; has a 6-month postintervention assessment; is appropriately powered; and uses an experimental working memory training intervention based on our current understanding of the cognitive mechanisms of training. Findings will inform future research and design of cognitive training interventions and highlight the value of the evidence-based principles of cognitive training.

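### The article says the trial will determine whether adaptive training is superior, but it describes and powers only comparisons with active control and concedes low power between training conditions

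*Protocol article*

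**What the plan says.** Two places state the conclusion without qualification. The Abstract's conclusions say: "This trial will determine whether the adaptive approach to setting the difficulty of training activities maximizes cognitive training outcomes for children". The last paragraph of the Discussion says: "This trial will determine whether the adaptive approach to setting the difficulty of working memory training activities is superior for maximizing training outcomes".

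The Statistical Analysis section enters "conditions (dummy coded with the active control as the reference) as the independent variables", and the effect sizes and confidence intervals are to show "the magnitude of differences in outcomes between each training condition relative to the active control". It then extends this: "The same analytic approach will be applied to secondary outcomes and to both primary and secondary outcomes at the 6-month postintervention time point". The Power Calculations section sizes the trial for each training condition against active control on near transfer (f² = 0.07, 80% power, 29 per condition, raised to 32 for attrition).

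Neither hypothesis under Aims and Hypotheses concerns adaptive against nonadaptive training. One is about transfer distance, the other about time since the intervention.

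The Discussion paragraph just before the superiority claim concedes that "this trial was not powered to detect potential differences between the adaptive, self-select, and stepwise working memory training conditions", and adds: "We anticipate the differences in effect sizes between the 3 conditions will be small, and therefore a particularly large sample size would be required".

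**The concern.** To be superior, or to maximize outcomes, adaptive training has to do better than the other ways of setting difficulty. Doing better than creative activities in the control arm shows only that adaptive training works. The described analysis gives three effects, each against the same control, and none of them is the difference between adaptive and another training condition. The article thus claims a property that its described design does not have, and two adjacent paragraphs of the Discussion conflict.

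At stake is the conclusion about adaptivity. With only control-referenced results, readers are left to set three P values or three effect sizes side by side. A difference in significance is not a significant difference, and three noisy estimates sharing one control will often look different when the underlying effects are the same.

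**Working it through.** **1. What the sample size covers.** Inputs from Power Calculations: f² = 0.07, α = .05, 80% power; two-sided from Statistical Analysis. Treat it as a test of one regression coefficient (noncentral F, 1 numerator df, noncentrality f² × N). The smallest N is 115, or 28.75 per arm, rounded up to 29. Power at N = 116 is 0.806, so the figure of 29 reproduces. A 3-df test of any difference among conditions would need N = 160 (40 per arm). The calculation therefore fits a single training-versus-control coefficient.

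**2. Precision of a direct contrast.** Adaptive minus self-select (or minus stepwise) comes from the same model, with 29 children in each arm. Residual df = 116 − 7 = 109 (intercept, three conditions, baseline score, two terms for three age strata). In units of the outcome SD, with baseline correlation r (not given in the article; assumed 0, 0.5 or 0.7):

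- SE = √(2/29) × √(1 − r²) = 0.263 × √(1 − r²)
- 95% CI half-width = t(.975, 109) × SE = 1.982 × SE
- Noncentrality for a difference d is d/SE. The article calls the expected difference small but gives no number, so d = 0.1 to 0.3 is assumed.

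| r | half-width (SD) | power, d = 0.1 | d = 0.2 | d = 0.3 |
|---|---|---|---|---|
| 0 | 0.52 | 7% | 12% | 20% |
| 0.5 | 0.45 | 7% | 14% | 26% |
| 0.7 | 0.37 | 8% | 18% | 35% |

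With all 32 per arm retained and r = 0, the half-width is 0.50 SD. For 80% power with 29 per arm, the true difference would have to be about 0.74 residual SD. Conversely, detecting 0.2 SD with 80% power needs 393 per arm at r = 0 or 201 at r = 0.7. This agrees with the article's own remark that a particularly large sample would be needed.

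**3. What control-referenced results look like when the approaches are identical.** Assume the same true effect in all three training arms, equal arm sizes and one shared control. Each test statistic is z = δ + (e_arm − e_control)/√2, with e standard normal and δ = 1.96 + z(power), that is 2.80 at 80% and 2.21 at 60%. The statistics correlate 0.5 through the control. An arm is significant if z > 1.96. Simulated proportions:

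| Power per arm vs control | Arms disagree on significance | Adaptive significant, at least one other not | Adaptive alone significant |
|---|---|---|---|
| 60% (assumed) | 48% | 25% | 7% |
| 80% (planned) | 34% | 19% | 4% |
| 90% (assumed) | 20% | 12% | 2% |

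The remaining disagreements run the other way. At 80% power, 34% − 19% = 15% of trials have adaptive non-significant while another training arm is significant. The 60% row is an assumption but not an extreme one: the near-transfer effect of g = 0.50 cited in the Introduction, 29 per arm and r = 0.5 give 59%.

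**The case against.** The formal aim, in the Abstract and under Aims and Hypotheses, is exploratory and is worded as a comparison with active control. The hypotheses, power calculation and model are consistent with that aim, and the lack of power between training conditions is openly disclosed. All of this stands, and it limits the weight of the point. It does not reconcile the claim with the concession, because the disclosure is followed at once by the unqualified statement, and the Abstract carries the claim with no caveat. Aims and Hypotheses also opens by presenting the trial as a test of the assumption that training should be adaptive.

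A reader might infer that the plan will judge adaptivity by which arms reach P < .05. No section says so. Statistical Analysis promises effect sizes, confidence intervals and Bayesian evidence, and says interpretation will weigh the strength of effects as well as P values. However, the effect sizes and intervals are tied to control, and the Bayesian methods are not tied to any comparison between training conditions.

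A reader might also infer that no such contrast will be run at all. The article supports only that none is described. The analysis plan is not shown and could add one, which needs no refitting. That would not remove the conflict between the claim and the conceded lack of power.

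Finally, the contrasts in the fix would themselves have low power. True: they would give an honest estimate with its uncertainty, not a settled answer.

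**Conclusion.** The point holds. The superiority claims in the Abstract and Discussion go beyond what the article describes and powers, and conflict with its own concession. A direct contrast would carry a margin of about ±0.37 to ±0.52 SD, so an inconclusive result could not exclude a small or moderate advantage in either direction. Power for a 0.2 SD difference is 12% to 18%. These figures rest on 29 analysed per arm and an assumed baseline correlation of 0 to 0.7.

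The risk from reading the control comparisons side by side is real but should not be overstated. With identical approaches, the arms disagree on significance in about 34% (80% power) to 48% (60%) of trials. The pattern that most suggests adaptive superiority, adaptive alone significant, arises in only about 4% to 7%. The stronger reading, that the trial would often wrongly declare adaptive better, is not supported.

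The primary comparisons with control are unaffected. This should be fixed, but it is not a fatal defect.

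**What to change.** - From the model already planned for each primary outcome, report adaptive minus self-select and adaptive minus stepwise, each with estimate, 95% CI and Bayes factor.
- Label these contrasts exploratory and date their addition, because the Results section says data collection is complete and analysis is under way.
- State that any conclusion about adaptivity rests on these contrasts only, not on comparing the three results against control.
- In the Abstract's conclusions and the Discussion, replace the claim to determine superiority with a statement that the trial will estimate the difference between adaptive and each nonadaptive approach with limited precision, about ±0.4 to 0.5 SD.

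The cost is two extra low-power contrasts per outcome and a less favourable stated conclusion. No new data or model are needed.
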